#### Sub-group analyses

Subgroup analyses are not powered for in this trial analysis but will be included and interpreted as exploratory only. Key pre-specified moderators of interest are area deprivation and ethnicity. If numbers allow, a group moderator interaction term will be added to the primary analysis model to investigate included moderator effects on treatment effectiveness. Other moderators to be considered for exploratory analysis include age group, sex, fall risk category and level of education.

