	**Participants**
**Inclusion criteria**	• Adults aged 65 or older who are not in full-time employment • Being at risk of major mobility disability (score between 4 and 9 (inclusive) on the Short Physical Performance Battery (SPPB)^a^ • Planning to reside in the target area (West Midlands, Greater Manchester, South Wales or Bristol) for at least 18 months
**Exclusion criteria**	• Self-reported high level of mobility^b^ or SPPB score above 9 at baseline screening • Self-reported inability to walk across a room without a walking aid other than a walking stick, or using a wheelchair or Zimmer frame • Existing major mobility limitation (defined as SPPB of 3 or less, or unable to complete the 4-m walk component of SPPB) • Living in residential or nursing care • Inability to meet regularly with an ACE volunteer • A documented or patient-reported medical condition that would preclude participation, including: o Severe arthritis that prevents participation in physical activity; o Parkinson’s disease or diagnosed dementia o Any terminal illness o Lung disease requiring use of orally administered corticosteroids or supplemental oxygen o Severe kidney disease requiring dialysis o Severe heart disease or an implanted cardiac defibrillator o Cardiac arrest which required resuscitation o Receiving radiation therapy or chemotherapy treatment for cancer o Awaiting knee or hip surgery o Major heart surgery in the last 6 months o Unstable heart condition (e.g. uncontrolled arrhythmia, angina, heart failure or hypertension) o Spinal surgery in the last 6 months o Any other clinical condition that the person’s GP or clinician considers would make them unsuitable for participation in an exercise programme
**Temporary exclusion criteria**	• Heart attack (or myocardial infarction), stroke, spinal surgery, hip fracture, hip or knee replacement within the previous 6 months • Currently receiving physical therapy on legs or enrolled in another physical activity research or intervention study

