### Randomisation/allocation

Eligible participants will be randomised to one of the two arms in a 1:1 ratio stratified by site (West Midlands, Greater Manchester, South Wales and Bristol), using a centralised web-based system run by the Cardiff University Centre for Trials Research (CTR).

To perform randomisation an authorised member of the research team will access the randomisation website using unique username and password log-in details. The website will require entry of patient’s initials, date of birth and stratification variable. The randomisation website will also generate a unique study ID number for the participants when they are randomised. In the relatively unlikely event that two people from the same household present for screening, to avoid the potential for contamination (if they were allocated to different groups), only the first would be included in the study. This, and the reasoning behind it, will be carefully explained during the telephone screening process.

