#### Adjusted analysis

While we are not expecting a significant imbalance between groups, variables such as age and biological sex may be considered for inclusion in the primary model.

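### If age is examined as a moderator, banding it discards information that date of birth already supplies; age in years would serve better, with bands for display only

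*Protocol article*

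**What the plan says.** The protocol article, Sub-group analyses, names area deprivation and ethnicity as the key moderators. It then adds: "Other moderators to be considered for exploratory analysis include age group, sex, fall risk category and level of education". The method is an interaction in the primary model, on a condition: "If numbers allow, a group moderator interaction term will be added to the primary analysis model". The status of all these analyses is stated openly: "Subgroup analyses are not powered for in this trial analysis but will be included and interpreted as exploratory only".

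Three other places bear on the point:

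- Randomisation/allocation: the randomisation website requires the participant's "initials, date of birth and stratification variable", so exact age at entry is known for everyone randomised.
- Table 1 admits "Adults aged 65 or older who are not in full-time employment" and sets no upper age limit, so age can vary widely.
- Adjusted analysis refers to age without grouping: "variables such as age and biological sex may be considered for inclusion in the primary model".

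The number of age groups and their boundaries are not given.

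**The concern.** A banded moderator assumes that the treatment effect is constant within each band and changes abruptly at each boundary. If the effect in fact rises or falls gradually with age, the age-by-arm term is estimated less precisely than the data allow, and its size depends on where the boundaries lie. Little precision can be spared, because the article already concedes that these analyses lack power. The exact variable is in hand, and the interaction model that the article describes accepts it without further change.

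At stake is the quality of one exploratory result: a wider interval for moderation by age than necessary, and an estimate that is harder to interpret.

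**Working it through.** **1. The article's own figure.** Sample size calculation gives a difference of 0.5 SPPB points, SD 1.56, 90% power, 5% significance and 206 per arm.

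- Normal approximation: n = 2 × (1.960 + 1.282)² × 1.56² / 0.5² ≈ 204.6, so 205 per arm.
- Noncentral t: 206 is the smallest n that reaches 90% (90.06%).
- With 20% loss: 412 / 0.80 = 515.

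The stated sample size reproduces. It concerns the main comparison; the article gives no figure for any moderator test.

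**2. Measure of the loss.** Suppose the treatment effect is linear in age A. If a banded version g(A) replaces A in the interaction, the share of information kept is

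R = corr(A, g(A))²,

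and the standard error on the same scale grows by 1/√R. R does not depend on the outcome SD. For a two-way cut of a normal variable at standardised point c, with a proportion p above it, R = φ(c)² / [p(1 − p)].

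- Median split: 0.3989² / 0.25 = 0.637, a loss of 36%.
- 80/20 split: 0.280² / 0.16 = 0.49, a loss of 51%.

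For a uniform variable R = 3p(1 − p): 0.75 at the median and 0.48 at 80/20.

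**3. Range over age distributions.** All five distributions are assumptions, because the article gives none. Each was simulated with 2,000,000 draws. Entries are the percentage of information lost. The 80/20 cut places the oldest fifth in the upper group.

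| Assumed age distribution | Bands <75, 75–84, 85+ | Median split | 80/20 split |
|---|---|---|---|
| Normal, mean 78, SD 7 | 21 | 36 | 51 |
| Normal (76, 8) truncated to 65–100 | 17 | 34 | 45 |
| Uniform, 65–90 | 14 | 25 | 52 |
| 65 + exponential (mean 10), capped at 100 | 14 | 44 | 30 |
| 65 + gamma (shape 1.5, scale 5) | 22 | 47 | 36 |

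The three-band entries score the bands as an ordered trend. Fitting them as unordered categories spends a further degree of freedom.

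The matching increases in standard error are:

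- three bands: 1/√0.86 = 1.08 to 1/√0.78 = 1.13;
- median split: 1/√0.75 = 1.15 to 1/√0.53 = 1.37;
- a 52% loss: 1/√0.48 = 1.44.

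**4. Illustration in power.** Take 412 analysed, 1:1 allocation, SD 1.56 and normal age. The standard error of the interaction per SD of age is 2 × 1.56 / √412 = 0.154. For an assumed change of 0.35 SPPB points per SD of age, power is Φ(0.35√R / 0.154 − 1.96):

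- age in years (R = 1): 62%;
- three groups (tertiles, R = 0.793): 53%;
- median split (R = 0.637): 44%. Here 412 participants carry the information of about 412 × 0.637 = 262.

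The value 0.35 is chosen only for illustration, and 1.56 is the baseline SD. The planned mixed model may leave a smaller residual SD, which would change the powers but not R.

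**The case against.** The strongest reply is that this is a modelling preference about an optional item. Age is only to be considered, it is not one of the two key moderators, the interaction is fitted only if numbers permit, and the result is declared exploratory. A condensed article may leave coding to an analysis plan that is not shown. All of this is correct and keeps the point small. It does not remove it, because the point concerns the form that the article states. The absent cut-points are not criticised. Fixing them in advance would prevent a data-driven choice of boundary but would not recover the lost information.

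A second reply is that the loss depends on linearity. If the effect changes at a threshold, a boundary near it need not lose this much, and a straight line would be the wrong model. This also stands. It is the reason for a non-linear check, which itself uses degrees of freedom in a weak test.

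Three stronger readings are tempting but unsupported:

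- A reader might infer that about a third of the information is the most that could be lost. The one-third figure belongs to a median split under roughly normal age. Three bands lose less, and an uneven two-way cut can lose more.
- A reader might infer that the plan commits to a grouped age test. Its wording does not go that far.
- A reader might extend the criticism to other moderators, such as fall risk category. The article does not show that any of them is held on a continuous scale and then banded.

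**Conclusion.** The point holds as a minor improvement. The article names grouped age as a possible moderator while exact age is held for everyone randomised. If the effect varies linearly with age, banding loses roughly 14 to 22% of the information with the three bands examined, roughly 25 to 47% with a median split, and up to about half with an uneven two-way cut among the cases examined. These ranges rest on assumed age distributions and assumed boundaries, since the article supplies neither, and they are not formal bounds. If moderation by age follows a threshold, the loss may be smaller. The main treatment comparison and the sample size of 515 do not depend on this choice.

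**What to change.** In Sub-group analyses, replace the grouped term with age in years. State that, if age is examined as a moderator, the age-by-arm interaction will use age as a continuous variable, with a non-linear term (for example a spline) as a check. Age bands can be kept for tables and plots, beside model-based treatment effects at a few chosen ages.

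The change needs a short edit and no new data. It adds a modest amount of analysis, namely the non-linear check and the effects at chosen ages. The non-linear term should be presented as a check on the shape, because it will have less power than the linear term if the relation is close to linear.

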#### Adjusted analysis

While we are not expecting a significant imbalance between groups, variables such as age and biological sex may be considered for inclusion in the primary model.

### Economic evaluation

The economic evaluation will estimate the incremental cost and incremental benefits of the ACE intervention compared to control, from a societal perspective. A within-trial analysis will estimate the cost-effectiveness at 18 months. A longer-term analysis will estimate the cost-effectiveness using a decision analytic model.

The within-trial analysis will adopt a micro-costing approach to estimate the costs related to the intervention. Study logbooks, questionnaires and volunteers’ time and travel diaries will collect resource use information at baseline, 6, 12 and 18 months for volunteer and participant time and travel, and health and social care use. Associated training costs will also be measured and reported separately. The resource use will be combined with unit cost data obtained from published sources such as the NHS reference costs [22], the British National Formulary [23] and the Prescription Cost Analysis [24] for England. Volunteer and participant time will be converted to costs using the value of leisure time. The primary outcome measure for the economic analysis will be quality-adjusted life year (QALYs) derived from utility scores, obtained from the EQ5D-5L instrument [25], and measured using the area-under-the-curve approach. Secondary economic outcomes will be Years of Full Capability (YFC), obtained from the ICECAP-O measure [26]. Both QALYs and YFC will be measured for the participants and volunteers. Any differences in baseline utility and capability index scores will be adjusted for in the analysis.

The economic evaluation will take the form of a cost-utility analysis (CUA) where the result will be expressed as a ‘cost per QALY’. In addition, a ‘cost per capability’ (CCapA) achieved will be estimated by combining the cost with improvements in capability. The analysis will report results of the CUA and CCapA from a health and social care perspective, including costs related to health and social care and QALYs/Capabilities accruing to the participants. Then, the analysis will be broadened to take a societal perspective including societal costs and outcomes for both participants and volunteers. Missing data will be explored and imputed using the most appropriate imputation technique that will depend on the nature of the missingness. Sensitivity analysis will be conducted to explore any uncertainties surrounding the key parameters using bootstrapping methods to estimate confidence intervals around the incremental cost-effectiveness. Cost-effectiveness acceptability curves will be generated to estimate the probability of the ACE intervention being cost-effective at different threshold willingness to pay values for a QALY. CHEERS guidelines will be followed for reporting the economic evaluations [27].

If the ACE intervention shows superiority in terms of improvements in mobility, we will conduct evidence synthesis and decision-analytic modelling to assess the lifetime cost-effectiveness of the intervention versus control, including consequences in terms of health and social care costs. Methods will follow best practice guidelines for decision-analytic modelling in health technology assessment [28].

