### Sample size calculation

The ACE trial will recruit a total of 515 participants across four study sites.

Effect Size: The primary aim is to assess the long-term (18-month) effect of a peer volunteering/physical activity intervention on changes in SPPB scores. A difference of 0.5 points in the SPPB score has been defined as a minimum clinically meaningful change [8, 19].

Using baseline data from 777 adults with the same inclusion criteria as we propose for this study (from our REACT trial [20, 21]), the standard deviation for SPPB scores in this population is 1.56. This is identical to the standard deviation observed for SPPB scores in the US-based LIFE trial (SD = 1.6, *N* = 1635). To detect a difference of 0.5 points in SPPB with 90% power and 5% significance, 206 participants are required per arm. Assuming a 20% loss to follow-up at 18 months [based on a 19% loss to follow-up at 24 months in our REACT study], the total sample size required is 515.

We will recruit a minimum of 130 volunteers (aged 55 + years) to support two intervention participants each. Since the cluster sizes in the intervention arm are minimal (less than two participants to each volunteer on average) we will not inflate the sample size required for clustering at the level of volunteer. However, the analytic strategy will present results from a partial cluster model to assess the small amount of possible clustering in the intervention arm only.

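### A bootstrap interval for cost per QALY or cost per capability cannot be interpreted if the effect difference is not clearly separated from zero; intervals for net monetary benefit would avoid this

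*Protocol article*

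**What the plan says.** All of this is in the Economic evaluation section of the protocol article.

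- **Horizon and outcome.** "A within-trial analysis will estimate the cost-effectiveness at 18 months". The main economic outcome is "quality-adjusted life year (QALYs) derived from utility scores, obtained from the EQ5D-5L instrument", and differences in baseline utility and capability scores are to be adjusted for.
- **Form of the result.** The cost-utility analysis is one "where the result will be expressed as a ‘cost per QALY". Alongside it, "a ‘cost per capability’ (CCapA) achieved will be estimated by combining the cost with improvements in capability". No other summary that combines cost and effect is named.
- **Uncertainty.** Sensitivity analysis is planned "using bootstrapping methods to estimate confidence intervals around the incremental cost-effectiveness". The next sentence adds: "Cost-effectiveness acceptability curves will be generated to estimate the probability of the ACE intervention being cost-effective at different threshold willingness to pay values". That sentence ties the thresholds to a QALY and does not mention capability.

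The section does not mention net monetary benefit, or what happens to replicates in different quadrants of the cost-effectiveness plane. It does not write the word ratio, and it does not name a type of bootstrap interval.

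**The concern.** Both named results are a cost difference divided by an effect difference. Such a ratio is discontinuous where the denominator passes through zero, and its sign does not tell the reader which option is better. For illustration, saving 300 and gaining 0.02 QALY gives −300 / 0.02 = −15,000. Costing 300 more and losing 0.02 QALY gives 300 / −0.02 = −15,000 as well. The first is the best possible result and the second the worst. An interval that ranks replicates by their ratio places them together.

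Cost-effectiveness is one of the two things the trial sets out to test. The lifetime model is to be built only if the intervention is superior on mobility. If it is not, the within-trial analysis is the only economic result, and a QALY difference near zero is then quite plausible. For the capability result, this interval is the only uncertainty summary the article states.

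**Working it through.** **1. The plan's own figure.** The Sample size calculation section sets its target thus: "To detect a difference of 0.5 points in SPPB with 90% power and 5% significance". With SD 1.56 and a two-sided test, n per arm = 2 × (1.960 + 1.282)² × 1.56² / 0.5² ≈ 204.6, so 205 (stated: 206). With 20% loss, 412 / 0.80 = 515, as stated. The size is therefore reproduced, but it is set on SPPB. No economic quantity enters it.

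**2. Inputs for the check.** From the article: 206 analysed per arm, borrowed from the SPPB calculation. Assumed, because the article gives none of them: 18-month QALY SD of 0.15, 0.25 or 0.35; QALY gain of 0.02 to 0.10; cost difference 300 with SD 4,000; threshold 20,000 per QALY; cost and QALY differences independent and normal.

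**3. Share of replicates at or below zero.** SE = SD × √(2/206) = SD × 0.0985, and the share is Φ(−gain / SE), without baseline adjustment.

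| SD | SE | gain 0.02 | gain 0.03 | gain 0.05 |
|---|---|---|---|---|
| 0.15 | 0.0148 | 8.8% | 2.1% | below 0.1% |
| 0.25 | 0.0246 | 20.8% | 11.2% | 2.1% |
| 0.35 | 0.0345 | 28.1% | 19.2% | 7.4% |

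**4. When a 95% ratio interval exists at all.** The Fieller interval is bounded only if the QALY difference exceeds 1.96 × SE. That is 0.029 (SD 0.15), 0.048 (SD 0.25) or 0.068 (SD 0.35). The difficulty thus depends on the difference relative to its standard error, and it is not a quirk of one bootstrap method.

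**5. Three cases, from 200,000 simulated replicates at SD 0.25.**

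| Gain | Gain / SE | Percentile limits of ratio | Fieller limits | Net monetary benefit |
|---|---|---|---|---|
| 0.02 | 0.81 | −173,751 to 193,312 | unbounded | −1,141 to 1,334 |
| 0.05 | 2.03 | −20,040 to 52,702 | −15,533 to 193,119 | −540 to 1,936 |
| 0.10 | 4.06 | −5,161 to 12,907 | −5,109 to 12,933 | 468 to 2,940 |

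At a gain of 0.02, 17.7% of replicates are cheaper and more effective, and 16.1% are dearer and less effective. So 33.8% of replicates have a negative ratio, split almost evenly between opposite conclusions. Net monetary benefit (20,000 × QALY difference − cost difference) has mean 20,000 × 0.02 − 300 = 100, a finite and ordered interval, and a probability of being cost-effective of 0.56.

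At about 2 SE the two kinds of ratio limit still disagree widely. They agree closely from about 3 SE: at SD 0.35 and gain 0.10 (2.9 SE) they are −5,720 to 16,300 and −5,604 to 16,651.

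**6. Baseline adjustment.** If QALYs correlate r with baseline utility, SE shrinks by √(1 − r²). At an assumed SD of 0.30 and r of 0.5 to 0.7 (factor 0.866 to 0.714), the share at or below zero falls from 15.5% to 12–8% for a gain of 0.03, and from 4.5% to 2.5–0.9% for a gain of 0.05.

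**7. Capability.** The same argument holds with years of full capability in the denominator. No SD is given for that outcome either.

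**The case against.** The strongest reply has four parts.

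- **The article does not write ratio or percentile.** True. The ratio is an inference, though the only results named are two ratios. The percentile method is an assumption of the working, but the unbounded Fieller interval shows that the trouble lies in the quantity and not only in the method.
- **Detail may sit in a fuller plan that is not shown.** Interval type and handling of quadrants can properly be left there, and their absence is not held against the article. The point concerns the quantity that the article says will carry the interval.
- **The acceptability curves already serve the decision.** This stands for QALYs. At each threshold the curve is the share of replicates with positive net benefit, so it does not depend on the ratio. It does not extend to cost per capability, and it does not make a separately reported interval readable.
- **Net monetary benefit is one remedy among several.** Also true. Fieller limits are another, but they are unbounded in exactly the case at issue. The plane with acceptability curves would serve as well.

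A reader might go further and infer that the main uncertainty statement of the economic analysis will be meaningless in the likeliest scenario. The article does not support that. It places the interval under sensitivity analysis, gives no expected QALY gain or SD, and plans baseline adjustment.

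**Conclusion.** The point holds conditionally. Read naturally, the article plans an interval for a ratio, and that interval cannot be interpreted if the effect difference is within about 2 standard errors of zero. It is usable when the difference is about 3 standard errors or more from zero. A design sized on SPPB does not exclude the bad case, but the article cannot show that it will occur.

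The size depends on the assumed QALY SD, the assumed gain and 206 analysed per arm. At SD 0.25 to 0.35 without adjustment, 21 to 28% of replicates fall at or below zero for a gain of 0.02, and 2 to 7% for a gain of 0.05. A smaller SD or baseline adjustment lowers these shares.

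The scope is the reporting of within-trial economic uncertainty. The SPPB analysis and the sample size are untouched.

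**What to change.** From the same bootstrap replicates:

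1. Report 95% intervals for incremental cost, incremental QALYs and incremental years of full capability.
2. Report 95% intervals for incremental net monetary benefit at the thresholds used for the acceptability curves, and show the cost-effectiveness plane.
3. Give each ratio as a point estimate. Add an interval only when the replicates lie clearly on one side of a zero effect difference; the working suggests about 3 standard errors as a guide.
4. Provide the same net-benefit or acceptability summary for the capability outcome, stating the range of values per year of full capability over which it is drawn.

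The cost is a sentence or two in the analysis plan and slightly more reporting. No new data, participants or model runs are needed.
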